### Study Design

2.1

This is a randomized, controlled cross-over clinical feasibility study. This study follows the CONSORT flow diagram extension for feasibility study [34]. The protocol has been written according to the Standard Protocol Items (SPIRIT checklist) [35].

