### Data collection

2.8

The data collection was made with a personal data sheet; consecutively the patients were enrolled at the Consultation and Psychosomatic Psychiatry Center of the University Hospital of Cagliari (San Giovanni di Dio Civil Hospital). The presence of possible side effects and satisfaction with the intervention was assessed through a self-report questionnaire, for the others, secondary outcome indicators were used, and a standardized evaluation tool validated in Italian and used in psycho-social research (in the case of a learning effect, different versions for retests were used). Participants were assessed before the treatment, after the end of the intervention, and after 6 and 12 months after the end of the intervention.

*For the cognitive evaluation was used:* Matrix test [38]; Rey Figure Test [39]; Rey's Words Test, in the two versions [40, 41]; Digital Symbol Substitution Test, in the two versions [42, 43]; Trail Making Test, in the two versions [44]; Normal and Inverse Digit Span, in the two versions [45, 46]; Stroop Test [47]; Frontal Assessment Battery - FAB [48]; Phonological and Semantic Verbal Fluency Test, in the two versions [41, 49]; Test of Cognitive Estimates (CET), in the two versions [50, 51]; Test of the Tale [52, 40].

*For the general evaluation was used:* SF-12, Short Form Health Survey with 12 items [53], a self-administering scale, which investigates the following dimensions of well-being: vitality, physical function, physical pain, perception of general health, mental health, physical and emotional, work functioning, and social role. TAS-20 Toronto Alexithymia Scale [54] self-administering scale, evaluates the level of emotional awareness. Self-Rating Scale (SAS) self-administered scale [55] evaluates perceived anxiety levels regardless of diagnosis. The Patient Health Questionnaire - PHQ-9, self-administering scale [56], evaluates depressive symptoms. Health of The Nation Outcome Scale - HoNOS [57] evaluates personal and social functioning and clinical performance. Biological Rhythms Interview of Assessment in Neuropsychiatry - BRIAN validated in Italian version [58], an interview consisting of 18 items that investigates 4 main areas related with the dysregulation of circadian rhythms (sleep, activity, social rhythms, and nutrition).

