### Data Analysis

2.10

The outcome of the trial was analyzed through multivariate analysis of variance (MANOVA). Through this procedure, the sample means of the dependent variables (scores in the performance tests) were compared in sub-samples divided by the two independent variables [time and group (intervention and non-intervention)]. For variables not on an interval scale, the analysis of variance for nominal data by De Castellan was used with a similar methodology.

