## CONCLUSION

Mental health is a fundamental resource that allows people to achieve daily goals in life and exercise the role of a citizen of a community. Bipolar disorder is recurrent condition that severely impacts the lives of people living with the experience; it is considered one of the leading causes of disabilities in the world [3]. To date, there is a lack of evidence for the treatment of cognitive deficits in BD even if cognitive deficits are a core component of personal and social functioning. The principle neuropsychological deficits are in attentional capacities, executive functions, and episodic/verbal memory [9]. The application of innovation science is increasing in the mental health field and the use of technologies can have a positive impact on psychiatric rehabilitation. The crossover study is a clinical study in which each group consecutively receives the treatments subjected to the study. This guarantees as an advantage a low variance given that the treatment and control correspond to the same participant (allows precise comparisons between multiple treatments) and it also guarantees the provision of the clinical intervention to all participants. The results of this study might have an impact on future studies, in particular, in the field of psychosocial intervention for the treatment of cognitive dysfunction in bipolar disorder and also in the technological innovation field for mental health rehabilitation.

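### Data Analysis (2.10) sends every variable not on an interval scale to a method for nominal data, so any ordered secondary outcome handled under that rule loses its ordering and some power

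*Protocol article*

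**What the plan says.** Section 2.10 (Data Analysis) gives two rules. The first is a MANOVA, and the quantities it takes as outcomes are "the sample means of the dependent variables (scores in the performance tests". As to the layout of that analysis, the article says that these means "were compared in sub-samples divided by the two independent variables [time and group (intervention and non-intervention". The second rule covers everything else: "For variables not on an interval scale, the analysis of variance for nominal data by De Castellan was used with a similar methodology". There is no third rule for ordered variables.

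Section 2.8 (Data collection) lists several rating instruments beside the cognitive tests, for example "The Patient Health Questionnaire - PHQ-9, self-administering scale [56], evaluates depressive symptoms" and, for a functioning rating, "Health of The Nation Outcome Scale - HoNOS [57] evaluates personal and social functioning and clinical performance". Satisfaction and side effects are collected by a self-report questionnaire. On timing, the section says: "Participants were assessed before the treatment, after the end of the intervention, and after 6 and 12 months after the end of the intervention".

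Section 2.1 (Study Design) states: "This is a randomized, controlled cross-over clinical feasibility study". The Conclusion gives as the advantage of this design a "low variance given that the treatment and control correspond to the same participant".

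**The concern.** The second rule is a positive instruction, not a gap left for a later document. It divides variables into interval and not interval, and gives the whole second class to a nominal method. Ordinal variables belong to that class. A nominal method asks only whether the category distributions differ. It gives the same answer whether patients moved up the scale, moved down it, or were rearranged without direction. The hypothesis in the Discussion is improvement, so direction is what the secondary outcomes need to show.

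The rule also takes over the layout of the first one, in which sub-samples are formed by time and group. That wording mentions no patient, pairing or period term. In a crossover, each patient supplies every time point and both conditions, and the benefit claimed in the Conclusion depends on using that pairing.

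At stake are power and interpretability for whichever ordered secondary outcomes fall under the rule.

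**Working it through.** **No figure to reproduce.** The article gives no alpha, power, effect size or SD. Its 50 participants were chosen for feasibility (section 2.11).

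**Inputs.** From the article: 50 randomised into two groups, four assessments, crossover. Assumed: 25 per group (no allocation ratio is stated), 3, 5 or 7 ordered categories of equal probability under no effect, a latent normal shift of 0.5 or 0.8 SD, within-patient correlation 0.5 or 0.7, and a two-sided 5% level. There were 4,000 runs per setting, so the Monte Carlo standard error is at most √(0.25/4000) = 0.8 points.

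**Nominal test.** The article gives no formula for the named procedure. The stand-in is a categorical analysis of variance with *n* observations, *k* categories and *g* groups:

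- TSS = n/2 − Σ(column total²)/(2n)
- WSS = n/2 − ½ Σ over groups of (Σ cell²/row total)
- R² = 1 − WSS/TSS
- C = (n−1)(k−1)R², referred to χ² on (k−1)(g−1) df

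**Step 1: does it use order?** Take two groups with counts (9, 7, 5, 3, 1) and (1, 3, 5, 7, 9), so n = 50 and every column total is 10.

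- TSS = 25 − 500/100 = 20
- WSS = 25 − ½(165/25 + 165/25) = 18.4
- R² = 1 − 18.4/20 = 0.08
- C = 49 × 4 × 0.08 = 15.68 on 4 df, p = 0.00348

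Shuffling the category labels leaves p at 0.00348. The statistic depends only on cell counts and has no sign, so it uses no order information.

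**Step 2: power between two independent groups of 25 at one time point**

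| Categories | Shift (SD) | Nominal | Rank-sum | Gap (points) |
|---|---|---|---|---|
| 3 | 0.5 | 26.9% | 33.1% | 6.2 |
| 3 | 0.8 | 58.4% | 66.3% | 7.9 |
| 5 | 0.5 | 24.3% | 37.9% | 13.6 |
| 5 | 0.8 | 55.0% | 72.5% | 17.5 |
| 7 | 0.5 | 22.2% | 37.8% | 15.6 |
| 7 | 0.8 | 51.9% | 74.5% | 22.6 |

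With no shift, rejection rates were 4.7% to 4.9% (nominal) and 4.6% to 5.7% (rank). The gap is therefore not explained by a difference in test level, apart from perhaps a point at seven categories.

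**Step 3: pre-post contrast in the same patients, if pairing is ignored** (5 categories)

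| Patients | Correlation | Unpaired nominal, no shift | Unpaired nominal, 0.5 SD | Signed-rank, 0.5 SD |
|---|---|---|---|---|
| 25 | 0.5 | 2.8% | 16.6% | 55.1% |
| 25 | 0.7 | 2.3% | 13.9% | 73.8% |
| 50 | 0.5 | 2.6% | 41.4% | 87.2% |
| 50 | 0.7 | 1.5% | 37.2% | 96.6% |

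The unpaired nominal test rejects too rarely under no effect (1.5% to 2.8%) and has far less power. The difference combines two losses, ordering and pairing.

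**The case against.** **Reach.** The article does not say which variables are non-interval. Summed scores such as PHQ-9 or HoNOS are commonly analysed as interval, and the nominal sentence could be aimed at plainly categorical items such as marital status, employment status or diagnosis (section 2.9). This objection stands. A reader might infer that power is lost on all the functioning and symptom outcomes, but the article does not support that. The only variables it names for MANOVA are performance-test scores, so the place of the rating scales is left open. Satisfaction is probably ordered, but satisfaction with the intervention has no usual-care counterpart, so the two-group figures do not carry over to it.

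**Pairing.** Time and group are called independent variables in the sense of factors, and a repeated-measures analysis could be described in the same words. The article is silent on pairing; it does not deny it. The wording belongs mainly to the MANOVA sentence, and error structure is commonly left to a fuller document. This stands too, so the pairing point is conditional.

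**False positives.** A reader might infer that repeated records inflate the type I error. With m records per patient, all in one group and pooled, P(|Z| > 1.96/√(1+(m−1)r)) at r = 0.7 gives about 13% for m = 2 and 27% for m = 4. Those figures should not be used here. Section 2.10 divides by time and by group, so a patient appears once in a cell, and the crossover puts each patient in both conditions. With one record per condition the corresponding expression for a mean-type contrast is P(|Z| > 1.96/√(1−r)). At r = 0.7 this is P(|Z| > 3.58), about 0.03%, which is conservative.

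**Stand-in and stakes.** The power gap depends on a stand-in statistic and assumed settings, and is only about 6 points with three categories and a 0.5 SD shift. The primary and coprimary outcomes are recruitment and completion proportions (section 2.7), and effectiveness is a preliminary secondary aim (section 1.1.2). All of this stands and limits the severity.

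The rule itself is not rescued. It covers all non-interval variables and makes no exception for ordered ones.

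**Conclusion.** The point holds in a limited form and is minor. As written, section 2.10 puts any ordinal outcome under a method that ignores order. That follows from the rule and from the nature of a nominal method, without simulation. Which outcomes are affected depends on a classification the article does not give: at least any ordered questionnaire items analysed under the rule, and the rating scales only if their totals are not treated as interval.

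The loss of about 6 to 23 points of power is illustrative. Its direction was the same in all six settings; its size rests on the assumed categories, shifts and 25 per group. If pairing is also ignored, the result for within-patient contrasts is conservatism and lost power. No claim of an inflated false-positive rate is supported. The feasibility conclusions are untouched.

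**What to change.** Amend section 2.10 to:

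1. Name the variables regarded as not on an interval scale, and say whether rating-scale totals are among them.
2. Keep the nominal method only for truly unordered variables.
3. Analyse ordered outcomes with a proportional-odds mixed model, with a patient random effect and terms for treatment, period and sequence. Another rank-based crossover analysis would also serve. A rank-sum comparison of the two sequences on within-patient period differences is simple, but it assumes that differences between ordinal scores can themselves be ordered.

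These terms describe the two treatment periods. The 6- and 12-month visits need their own sentence: after the one-month washout and three-month second period, group B finishes 1 + 3 = 4 months after group A, so by group A's six-month visit both groups have had the intervention.

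The cost is a sentence or two of wording and standard software. The small downside is the proportional-odds assumption, which a rank-based analysis avoids.

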### Sample Size Considerations

2.11

To date there is still poor evidence in this field of research for establishing an effective methodology in terms of sample size, and in this sense, the aim of this study is to verify the feasibility [20, 59]. We randomized 50 participants in order to be able to assess the feasibility outcomes: recruitment and retention rates Fig. (**1**).

### Trial Status

2.12

The study is registered on ClinicalTrials.gov (NCT05070065). The Regional Ethical Committee has approved the study (PG/2020/21681). The study started before the pandemic situation, after the lockdown, we had to interrupt the study. It was repeated and definitely started again in August 2021. Actually, the participants are receiving the VR-CR program.

## RESULTS

3

The results of the trial will be published in international peer-reviewed journals and will be disseminated at international meetings and congress.

## DISCUSSION

4

The primary aim of this trial is to study the feasibility (recruitment and retention rates to inform sample size calculations to confirmatory trials) of a VR-implemented CR tool (CEREBRUM), secondary to study cognitive and psychosocial variables. The hypothesis is that through a cognitive remediation virtual reality program, and using ecological instrument, it is possible to improve cognitive abilities and also the other social and personal outcomes. Their results were discussed with all the authors.

### Risk and Benefits

4.1

The use of immersive VR could have different side effects such as dizziness, nausea, headache, eye fatigue, reduced limb control, reduced postural control, reduced sense of presence, and development of inadequate responses to the real world. As a matter of fact, important side effects are not expected, as the VR tool has already been used in people with psychosocial disabilities, albeit for other purposes, without substantial side effects [60-64].

## CONCLUSION

Mental health is a fundamental resource that allows people to achieve daily goals in life and exercise the role of a citizen of a community. Bipolar disorder is recurrent condition that severely impacts the lives of people living with the experience; it is considered one of the leading causes of disabilities in the world [3]. To date, there is a lack of evidence for the treatment of cognitive deficits in BD even if cognitive deficits are a core component of personal and social functioning. The principle neuropsychological deficits are in attentional capacities, executive functions, and episodic/verbal memory [9]. The application of innovation science is increasing in the mental health field and the use of technologies can have a positive impact on psychiatric rehabilitation. The crossover study is a clinical study in which each group consecutively receives the treatments subjected to the study. This guarantees as an advantage a low variance given that the treatment and control correspond to the same participant (allows precise comparisons between multiple treatments) and it also guarantees the provision of the clinical intervention to all participants. The results of this study might have an impact on future studies, in particular, in the field of psychosocial intervention for the treatment of cognitive dysfunction in bipolar disorder and also in the technological innovation field for mental health rehabilitation.

## Figures and Tables

**Fig. (1) F1:**
[figure not shown]
CONSORT flow diagram extension for a feasibility study (stopped at the current trial status).

**Table 1 T1:** Gantt diagram of the study design.

**Month**	**1**	**2**	**3**	**4**	**5**	**6**	**7**	**8**	**9**	**10**	**After 6 Months from the Treatment**		**After 12 Months from the Treatment**	
**Recruitment**														
**Eligibility screen**														
**Informed consent**														
**Randomization**														
**Intervention**				**Group A**		**Group B**				
**Assessment**														
**Follow-up**														

## Data Availability

The authors confirm that the data supporting the findings of this study are available within the manuscript.

## LIST OF ABBREVIATIONS

CEREBRUM: = Cognitive Remediation Virtual Reality Program
VR: = Virtual Reality
SAS: = Self-Rating Scale
